### Randomisation and blinding

Randomisation will be carried out according to the International Council for Harmonisation guidelines [91]. Randomisation to one of the three trial arms will be conducted immediately after completion of the baseline assessment using a computerised randomisation procedure within the Black Dog Institute Research Engine. A stratified randomisation approach with a block size of 6 (1:1 ratio) will be used to ensure balance across the conditions in terms of age (12 to 14 years vs. 15 to 17 years), and symptom severity (mild [as determined by a total score of 9 or less on the PHQ-A] vs moderate to moderately-severe [as determined by a total score of 10 or more on the PHQ-A]). Allocation will be fully automatic, with no input from the research team. Participants will not be directly informed of their condition allocation; however, they may be able to deduce this based on differences in the study activities. For the primary outcomes analyses, the statistician will be blinded to participants’ allocations. The statistician will be unblinded when examining intervention completion rates due to differences in the total number of modules/lessons across each condition as well as when conducting exploratory moderator analyses. Key members of the research team not involved in data analysis, including research assistants providing guided support, will be unblinded to participants’ allocation as they will require access to the Black Dog Institute Research Engine to contact participants if they experience adverse events and to provide support to participants allocated to the guided use condition.

### Data collection, management and statistical methods

All participant data will be collected and stored on the Black Dog Institute Research Engine, hosted on secure servers commissioned by the University of New South Wales at GovDC Data Centres located in Sydney, Australia. The data is stored in a SQL Server 2016 database which is backed up daily. The Research Engine automatically generates a unique participant identification code, to enable the protection of participant confidentiality. For analyses, all study assessment data will be exported, via a Microsoft Excel file, from the Research Engine to SPSS Version 26. These files will be stored on UNSW OneDrive and deidentified by approved members of the research team. All identifiable information, including participant name, email address, mobile phone number, IP addresses, and free response data, and group allocation will be removed from the outcomes analysis file. This dataset will then be transferred to the trial statistician for analyses using a password protected OneDrive file. All identifiable study assessment data will only be accessible to the research team listed on the project, while aggregate deidentified data will be retained for future evidence synthesis.

Primary analyses will be conducted to determine the effect of the interventions on depressive symptoms at the primary and secondary endpoints. Analyses will be undertaken on an intention-to-treat basis, including all participants randomised, regardless of adherence or intervention received. The effectiveness of the trial interventions will be established by change on the PHQ-A between baseline and 6-weeks post-baseline (primary endpoint) and baseline and 4-month follow-up (secondary endpoint), based on the interaction between time and condition, using mixed-effects repeated measures linear modelling with an unadjusted *p* value of 0.05. The mixed-effect linear modelling will account for all available data, under the missing at random assumption. Effect sizes will be calculated based on differences in observed change scores between baseline and 6-weeks post-baseline, using standard deviations of the change scores pooled across conditions. Attrition analyses will be conducted to determine whether missing data is associated with any baseline demographics (age, gender), mental health status (symptom severity, past or current treatment) or other descriptive variables. Any baseline variables identified as substantially imbalanced between groups will be added to the models on an exploratory basis to confirm the robustness of the findings to this imbalance. Where distributional assumptions cannot be satisfied, other modelling may be used to confirm the robustness of the findings. Similar models will be used for secondary outcomes. To analyse the effects of adherence on outcomes, the mixed-effects repeated measures linear modelling will be repeated for each intervention condition separately using the categorical adherence measure as a between group factor (adherers v non-adherers v control). The categorial adherence measure has been selected for this analysis to determine whether instructions for use optimise benefit as intended or require adjustment. These results will be published in the primary outcomes paper. Exploratory analyses will examine evidence for moderation and mediation, that is, whether the intervention was more effective for certain subgroups of the sample (e.g., based on gender, baseline symptom severity, perceived need for help and openness to digital interventions) and whether the effects on outcomes were influenced by other variables, including rumination, emotion regulation, CBT skill acquisition, digital therapeutic alliance, and measures of app engagement. These results may be published in separate papers to appropriately describe the methods and analyses. A deidentified data set will be made available upon reasonable request at the discretion of the principal investigator.

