### Sample size

The total sample size required for detecting change in the primary outcome at the primary endpoint was calculated to be 489. This was based α = 0.05, power = 0.8, small to medium within-group effect sizes for psychoeducation (d = 0.10) [40, 41], self-directed CBT (d = 0.35) [89], and guided CBT (d = 0.65) [18, 19] on depressive outcomes and a conservative attrition rate of 20% between baseline and primary endpoint. This sample size will also be sufficient to detect small between-group effect sizes between the intervention conditions and the attention control condition and between the self-guided and supported use intervention conditions.

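### The primary PHQ-A test is fixed as a difference in change without baseline adjustment: unbiased, but less efficient than it could be, with a standard error that tends to be too large

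*Protocol article*

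**What the plan says.** The protocol article, under Data collection, management and statistical methods, states that "The effectiveness of the trial interventions will be established by change on the PHQ-A between baseline and 6-weeks post-baseline (primary endpoint") and, secondarily, to 4 months. The test is the time-by-condition interaction in a mixed-effects repeated-measures linear model using all available data under missing at random. Effect sizes are computed from observed change scores and their pooled standard deviation.

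Under Randomisation and blinding, a stratified scheme with blocks of 6 "will be used to ensure balance across the conditions in terms of age (12 to 14 years vs. 15 to 17 years), and symptom severity", with severity split at a PHQ-A total of 9 or less against 10 or more.

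The only rule on covariates is in the statistical methods section: "Any baseline variables identified as substantially imbalanced between groups will be added to the models on an exploratory basis". Baseline PHQ-A is not named as a covariate, no common baseline mean is mentioned, and neither stratification factor is named in the model. The data availability statement refers to a preregistered analysis plan, which is not shown.

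**The concern.** If baseline PHQ-A is a response occasion and each arm has its own baseline mean, the interaction at 6 weeks with complete data is exactly the difference in mean change. That estimator subtracts the whole baseline value even when follow-up depends on baseline with a slope below 1, which adds noise. Conditioning on baseline, or constraining the baseline means to be equal as randomisation justifies, removes that noise.

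Stratified allocation adds a second effect. It balances much of baseline PHQ-A between arms, so the change contrast truly varies less than a model without that information believes. The reported standard error is then too large and the test conservative.

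The stated covariate rule does not repair either effect. It selects after the data are seen, is exploratory only, and should rarely be triggered by variables that the randomisation balances. What is at stake is power and interval width, not validity.

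**Working it through.** **The plan's own figure.** The Sample size section gives alpha 0.05, power 0.8, "small to medium within-group effect sizes for psychoeducation (d = 0.10"), "self-directed CBT (d = 0.35"), "guided CBT (d = 0.65") and "a conservative attrition rate of 20% between baseline and primary endpoint". Two-sided testing is assumed. A two-sample t-test at d = 0.35 needs 130 per arm; 130/0.80 = 162.5, rounded up to 163; 3 × 163 = 489, the stated total. Only the roughly 130 completers per arm are carried forward.

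**General formula.** Let follow-up depend on baseline with slope b and residual SD s, and let baseline have SD Sx.
- Variance of change, per person: s² + (1 − b)²Sx²
- Variance after baseline adjustment: s²
- Ratio of reported variances: s² / [s² + (1 − b)²Sx²]

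With equal SDs at both times, b = r and s² = (1 − r²)Sx². The ratio becomes (1 − r²)/(2 − 2r) = (1 + r)/2, or 0.65, 0.75 and 0.85 at r = 0.3, 0.5 and 0.7.

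**Why that is an upper guide to the gain.** Entry is limited to PHQ-A 5 to 19 at screening while the outcome runs from 0 to 27, so the baseline SD is probably the smaller one. For the true sampling variance, stratification also replaces Sx² by something closer to the smaller within-stratum variance.

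**Simulation under this design.** Assumptions: baseline PHQ-A limited to 5 to 19, stratified allocation, 20% dropout, residual SD 4, a 1.2-point effect, and completer change score against baseline adjustment.

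| Slope b | True variance ratio | Reported variance ratio | Power gain (points) |
|---|---|---|---|
| 0.3 | 0.84 | 0.71 | 14 |
| 0.5 | 0.91 | 0.82 | 8 |
| 0.7 | 0.97 | 0.93 | 2 |
| 0.9 | 1.00 | 0.99 | 0 |

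The reported column can be checked by hand with s = 4 and an assumed Sx of 3.7 (Sx² = 13.69):
- b = 0.3: 16/(16 + 0.49 × 13.69) = 16/22.71 = 0.70
- b = 0.5: 16/(16 + 0.25 × 13.69) = 16/19.42 = 0.82
- b = 0.7: 16/(16 + 0.09 × 13.69) = 16/17.23 = 0.93
- b = 0.9: 16/(16 + 0.01 × 13.69) = 16/16.14 = 0.99

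With no treatment effect, the unadjusted change test rejected in about 3.3% to 3.9% of trials at slopes 0.3 to 0.5, below the nominal 5%.

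**Closer to the planned model.** A mixed model with unconstrained baseline means also uses dropouts' baselines, which recovers part of the loss. A simulation of that model (residual SD 3.5 to 4) gave these results for baseline adjustment against it:

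| Slope b | Reported variance ratio | Power |
|---|---|---|
| 0.3 | 0.77 | 57% to 69% |
| 0.5 | 0.83 to 0.87 | 62% to 69%, or 73% to 79% |
| 0.7 | 0.93 to 0.95 | 64% to 66%, or 76% to 78% |
| 0.9 | 0.99 | 66% to 66% |

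The unconstrained model overstated its standard error by 5% to 9% at slopes 0.3 to 0.5.

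**What the strata add.** Relative to the unconstrained mixed model, the true variance ratio was 0.87 with baseline PHQ-A alone and 0.87 with the strata added (slope 0.3), and 0.93 against 0.93 (slope 0.5). The change contrast with strata but without baseline PHQ-A gave 1.00 to 1.02.

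**The case against.** The strongest reply is that the article is silent rather than wrong. It gives a model class, and a mixed model of that class with a common baseline mean would already be the recommended analysis. Covariate lists are commonly left to an analysis plan, and one is said to be preregistered. This stands in part: the strata are not named, which is different from being excluded, and the unseen plan may settle the matter. But the article does commit to change through the interaction and does state a covariate rule, so the choice is not wholly deferred.

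Several stronger readings are tempting and not supported:
- **That the primary result would be biased or its type I error inflated.** A difference in change under randomisation is unbiased, and the test is conservative if anything. Raw change scores are specified only for the effect sizes; the test is a likelihood model.
- **That chance baseline differences enter at full weight.** Severity stratification removes much of them.
- **That the loss equals 54%, 33% or 18% more participants.** These are 1/0.65, 1/0.75 and 1/0.85 from the equal-SD formula, which does not fit restricted entry and stratified allocation.
- **That the stratifiers would return precision.** Severity is a dichotomised PHQ-A score and is nearly redundant once baseline is modelled.
- **That the self-directed contrast has 52% power.** The stated effect sizes imply 0.35 − 0.10 = 0.25 against control, but 52% holds only if that is in units of the SD of change, or equivalently r = 0.5. In raw-SD units with 130 per arm, the change test has 40%, 52% or 74% power at r = 0.3, 0.5 or 0.7. The sample size basis is a separate matter.

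**Conclusion.** The point holds as one of efficiency and of standard errors that match the design. The stated primary contrast, fitted in the usual way, gives up precision that the collected baseline PHQ-A would return, and at lower slopes it overstates its own standard error. Across assumed slopes of 0.3 to 0.9, adjustment cuts the reported variance by about 29% to 1% against a completer change score. Against a mixed model that keeps dropouts' baselines the cut is about 23% to 1%. The corresponding power gains are about 14 to 0 and 12 to 0 points. True sampling variance falls by less, about 16% to 0% in the completer comparison.

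These figures rest on an assumed slope, residual SD and baseline spread, none of which the article gives. They also assume that stratification uses the same PHQ-A score that serves as baseline; if it uses an earlier screening score, less of baseline is balanced. The benefit vanishes as the slope approaches 1. No stated figure is made wrong. The change is recommended rather than essential, and if the preregistered plan already constrains the baseline means and names the strata, one clarifying sentence is enough.

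**What to change.** Before unblinding, specify the primary model as follows:
- PHQ-A at baseline, 6 weeks and 4 months as the response, with time categorical.
- Baseline mean constrained equal across the three arms. Alternatively, use baseline PHQ-A by time as a covariate, handled so that every randomised participant is kept.
- Condition-by-time terms at 6 weeks and 4 months, with the 6-week contrasts as primary.
- Age stratum by time and severity stratum by time as fixed effects, included so that the analysis matches the randomisation and the standard errors are correct.
- Any adjustment driven by observed imbalance kept strictly as a sensitivity check.

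This costs a paragraph of analysis wording. It needs no new data and stays within the same class of mixed models, and it preserves the intention-to-treat set.

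### The effect size is taken from observed 6-week change scores, while the test uses a missing-at-random mixed model on all available data, so the two can disagree if dropout differs by arm

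*Protocol article*

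**What the plan says.** All of the relevant text is in the protocol article, under Data collection, management and statistical methods, apart from the attrition figure under Sample size.

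- **Population:** "Analyses will be undertaken on an intention-to-treat basis, including all participants randomised, regardless of adherence or intervention received".
- **Test:** effectiveness is judged on PHQ-A change, "based on the interaction between time and condition, using mixed-effects repeated measures linear modelling with an unadjusted" p value of 0.05.
- **Missing data in the test:** "The mixed-effect linear modelling will account for all available data, under the missing at random assumption".
- **Effect size:** "Effect sizes will be calculated based on differences in observed change scores between baseline and 6-weeks post-baseline".
- **Standardiser:** the difference is then scaled "using standard deviations of the change scores pooled across conditions".
- **Expected loss:** the Sample size section allows for "a conservative attrition rate of 20% between baseline and primary endpoint".

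The same methods section plans attrition analyses that ask whether missingness is related to baseline characteristics, symptom severity among them.

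**The concern.** The effect size is fixed on a narrower data basis than the test beside it. Anyone without a 6-week PHQ-A has no observed change score and drops out of the effect size, although their baseline score (and any 4-month score) stays in the model. A simple difference in observed change also needs a stronger condition than the model does: the participants who remain must be comparable between arms on whatever predicts change.

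That condition is not assured here. Contact differs by arm. Guided participants have weekly SMS sessions and 25 AUD at allocation, both app arms get reminders to use the app, and controls have no extra contact beyond the weekly flyer message unless they ask for technical help. If retention or its link to severity differs between arms, the paper could report a p value for one estimate and an effect size for another. Later evidence syntheses may use the standardised figure.

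**Working it through.** **How many participants.** The planned total is 489, or 163 per arm. A two-sided two-sample t-test at alpha 0.05 (sidedness assumed) and power 0.80, with a between-group d of 0.35, needs 130 per arm; 130 / 0.8 = 162.5, rounded up to 163, and 3 × 163 = 489. So the total is consistent with 20% loss applied as n / (1 − 0.2). (The article lists 0.35 as a within-group value; that is a separate matter.) At 20% loss, 489 × 0.8 = 391 have an observed 6-week change and 489 × 0.2 = 98 do not.

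**When the two estimates differ.** Put PHQ-A in SD units with equal SDs at both times and correlation r; the documents give neither r nor the SD. For a participant with standardised baseline b in an arm with mean reduction e, the expected reduction is e + (1 − r)b. Among those assessed, the arm mean is e + (1 − r)m, where m is the mean baseline of the assessed. With true difference δ:

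observed difference = δ + (1 − r)(m_app − m_control)

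d = observed difference / pooled SD of observed change

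The second term vanishes when m is the same in both arms. A mixed model that includes the baseline scores of everyone, with a suitable covariance structure, continues to target δ when dropout depends on baseline.

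**Numbers.** Assumptions: δ = 0.25, r = 0.5, dropout logistic in baseline with the slope shown (log-odds per SD). The values of m follow by numerical integration; the pooled SD of observed change is 0.99 to 1.00 throughout.

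| Control: rate, slope | App: rate, slope | m control | m app | Observed difference | d |
|---|---|---|---|---|---|
| 20%, 0.7 | 20%, 0.7 | −0.130 | −0.130 | 0.25 + 0.5(0) = 0.250 | 0.25 |
| 20%, 0.5 | 20%, 0.7 | −0.096 | −0.130 | 0.25 + 0.5(−0.034) = 0.233 | 0.235 |
| 10%, 0.7 | 30%, 0.7 | −0.067 | −0.191 | 0.25 + 0.5(−0.124) = 0.188 | 0.19 |
| 20%, 0 | 20%, 0.7 | 0 | −0.130 | 0.25 + 0.5(−0.130) = 0.185 | 0.19 (simulation: 0.18) |
| 10%, 0 | 30%, 0.7 | 0 | −0.191 | 0.25 + 0.5(−0.191) = 0.154 | 0.16 |
| 20%, 0.7 | 20%, 0 | −0.130 | 0 | 0.25 + 0.5(0.130) = 0.315 | 0.32 |

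The first row shows no divergence although dropout depends on severity. The third shows that unequal rates suffice when the severity slope is shared. The last shows overstatement. These are illustrations and not bounds: opposite slopes of 1 and −1 at 20% loss give 0.08.

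**Scale.** Dividing by the SD of change multiplies a raw-SD effect by 1/√(2(1 − r)): 0.85 at r = 0.3, 1.00 at r = 0.5, 1.29 at r = 0.7. Without r a reader cannot convert one to the other.

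**The case against.** The best defence is that nothing is decided on this effect size. Effectiveness rests on the time-by-condition interaction, and the effect size is one descriptive sentence after it. Reporting an observed-data summary beside a model-based test is common. The plan also examines attrition, and nothing in it points to severity-driven dropout in one arm only. With about 130 assessed per arm, the standard error of d is roughly √(2/130) = 0.12, so the shifts above (at most 0.09 from 0.25 in the table) are smaller than sampling error. All of this stands and limits the weight of the point. It does not remove it: a shift of this kind is systematic, does not shrink with sample size, and is avoided by using a model that is being fitted anyway.

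The standardiser is also defensible. The SD of change is a recognised choice, and the article states it openly. The baseline SD is not clearly better, because entry is restricted to PHQ-A 5 to 19 on a 0 to 27 scale, which can shrink that SD and enlarge d relative to unrestricted samples. This part stands: the choice is a convention, and what matters is naming it and allowing conversion.

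A reader might infer that the effect size will be off the scale of the values in the Sample size section (0.10, 0.35, 0.65). The documents do not support that. No standardiser is given for those values, a within-group d may itself use the SD of change, and nowhere is a comparison with them planned.

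**Conclusion.** The point holds as an inconsistency of data basis. The effect size covers about 391 of 489 participants if attrition is as planned, the model covers all randomised, and the two need different conditions on missing data. Under the assumed patterns the effect size is 0.16 to 0.32 against a true 0.25, about 0.24 for mild differences between arms, and 0.25 when rate and severity dependence match. These figures rest on r = 0.5, equal SDs, logistic dropout on baseline severity and a correctly specified model. If dropout depends on the unseen 6-week score itself, the model estimate can be biased too.

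Four stronger readings should be resisted:

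- The article does not call this its main result.
- The effect size does not undo the intention-to-treat analysis; that test is untouched.
- It is not restricted to people who completed the intervention. Non-adherers and those who never downloaded the app count if they answer at 6 weeks.
- It does not require data missing completely at random, and the direction of any error cannot be predicted from the documents.

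**What to change.** Replace the effect-size sentence so that the 6-week effect size comes from the primary model. Report the model-estimated difference in change for each comparison with its 95% confidence interval in PHQ-A points, and the same contrast divided by a named SD. Either standardiser will serve:

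- the baseline SD of all randomised participants, with a note that entry was restricted to PHQ-A 5 to 19; or
- the SD of change, with the baseline-to-6-week correlation reported so that readers can convert.

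Keep the observed-change d, if wanted, only as a supplement labelled observed-case, with the number contributing in each arm. No extra data are needed: the model is already planned, and baseline assessment precedes randomisation, so baseline scores should be available for everyone randomised. The cost is one sentence in the analysis section and minor analysis work.

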**Methods:**

We aim to recruit 489 adolescents aged 12-17 years with mild to moderately-severe depressive symptoms. Participants will be screened for inclusion, complete the baseline assessment and are then randomly allocated to receive ClearlyMe® (self-directed use), ClearlyMe® with guided SMS support (guided use) or digital psychoeducation (attention-matched control). Depressive symptoms and secondary outcomes will be assessed at 6-weeks (primary endpoint) and 4-months post-baseline (secondary endpoint). Engagement, conceptualised as uptake, adherence and completion, will also be assessed 6-weeks post-baseline. Mixed-effects linear modelling will be used to conduct intention-to-treat analyses to determine whether reductions in depressive symptoms and secondary outcomes are greater for conditions receiving ClearlyMe® relative to control at 6-weeks and 4-months post-baseline and greater for intervention adherers relative to non-adherers. To minimise risk, participants will be encouraged to use the Get Help section of the app and can also opt to receive a call from the team clinical psychologist at baseline, and at the 6-week and 4-month post-baseline assessments when reporting suicidal ideation.

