#### Engagement – ClearlyMe®

The current study utilises and will report multiple measures of engagement, consisting of ‘uptake’, ‘adherence’, and ‘completions’. In the current study, ‘uptake’ is defined as the proportion of participants (%) who take up the app, measured by app downloads. ‘Adherence’ is defined as the proportion (%) of participants who followed the instructions for app use. This will be measured in two ways: 1) A categorical variable (adherers vs. non-adherers) in which participants who complete at least one collection each week for the entire 6 weeks will be deemed ‘adherers’; 2) A numerical variable in which participants will earn 1 point for each week that they adhered to the instructions (i.e., completed at least one collection) resulting in a total adherence score (range: 0 to 6). ‘Completions’ is used to describe participants’ exposure to the app content, measured in three ways: 1) the number of lessons completed as a proportion of the total number of lesson, 2) the proportion (%) who completed more than half of the app content (i.e, 19 of 37 lessons), 3) the proportion (%) that completed all of the app content (i.e., all 37 lessons). Additional exploratory data will be collected to describe participants’ use of the ClearlyMe® app: collections completed (out of 9), the total number of times app features are accessed (e.g., Stories, View all, Get help now, Mood check, Saved), time spent in app (minutes), the collections and lessons liked/disliked, the collections and lessons saved, and individual responses to the lesson activities. Different measures of engagement have been employed to move beyond the pervasive conceptualisation of engagement as the ‘more use, the better’ in acknowledgement that there are multiple ways participants may engage with the intervention [38, 87, 88]. Recommendations have been followed [88] to include measures frequently used in the literature (e.g., proportion of lessons completed), intervention specific measures (e.g., frequency of feature access) and a measure of adherence defined as the extent to which actual use aligns with instructions for use. This allows a deeper analysis of the most beneficial way to use ClearlyMe® and supports comparisons with other studies given the heterogeneous reporting of engagement [36, 38, 88].

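### The adherer versus non-adherer comparison is labelled intention-to-treat although it is not randomised, and alone it cannot show whether the instructions for use work

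*Protocol article*

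**What the plan says.** In the Abstract (Methods), one sentence begins "Mixed-effects linear modelling will be used to conduct intention-to-treat analyses to determine whether reductions in depressive symptoms and secondary outcomes are greater" for the app conditions relative to control, and ends "and greater for intervention adherers relative to non-adherers". Both comparisons therefore sit under the same intention-to-treat label.

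The section on data collection, management and statistical methods describes intention-to-treat as "including all participants randomised, regardless of adherence or intervention received". It later says that the mixed model will be repeated for each intervention condition separately, "using the categorical adherence measure as a between group factor (adherers v non-adherers v control"). The stated purpose is "to determine whether instructions for use optimise benefit as intended or require adjustment". The results are to go into the primary outcomes paper. Only the moderation and mediation analyses that follow are called exploratory.

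Adherence is defined under Engagement – ClearlyMe®: "participants who complete at least one collection each week for the entire 6 weeks will be deemed" adherers. Everyone else in the app arms is a non-adherer. No corresponding split is defined for control.

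**The concern.** There are two separate problems.

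The first is the label. An analysis that disregards adherence cannot also group participants by adherence. A reader who has only the Abstract would take the adherer comparison to have the protection of randomisation, which it does not have.

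The second is the inference. Whether someone is an adherer is decided by that person after allocation and is known only when the six weeks are over, which is when the primary outcome is measured. Whatever makes a participant keep going (motivation, how symptoms are developing, stable circumstances) may also bear on recovery. Control contains people who would and would not have adhered, all in one group, so adherers are a selected subset set against an unselected arm. The contrast mixes any effect of adhering with the kind of person who adheres. Yet it is meant to decide whether the instructions deliver benefit or need changing, and it will be printed beside the randomised result.

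**Working it through.** **The label.** The Abstract lists adherers versus non-adherers as an aim of the intention-to-treat analyses. The statistical methods section defines that basis as disregarding adherence. Both statements cannot hold for the same comparison.

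**Size of the possible bias with an inert app.** The plan gives no figure of its own to reproduce here.

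Inputs from the protocol (Sample size; Trial design):
- 489 participants, equal allocation: 489/3 = 163 per arm.
- 20% attrition: 163 × 0.8 = 130.4, about 130 per arm analysed.
- α = 0.05, taken as two-sided.

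Assumptions, because the documents give no values:
- Proportion of adherers p = 0.30.
- Correlation ρ between tendency to adhere and natural improvement = 0.1, 0.2 or 0.3.
- Standardised change scores (SD 1), the same mean in both arms and no app effect.

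Adherers are those whose latent tendency exceeds the cut c that leaves 30% above it. So c = 0.524 and the normal density there is φ(c) = 0.348. The expected gaps are:
- adherers minus control = ρφ(c)/p
- non-adherers minus control = −ρφ(c)/(1 − p)
- adherers minus non-adherers = ρφ(c)/[p(1 − p)]

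For ρ = 0.2 these are 0.2 × 0.348/0.30 = 0.23; −0.2 × 0.348/0.70 = −0.10; and 0.2 × 0.348/0.21 = 0.33.

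With 39 adherers, 91 non-adherers and 130 controls, the standard errors are √(1/39 + 1/91) = 0.191 and √(1/39 + 1/130) = 0.183. For ρ = 0.2 the expected z values are 0.331/0.191 = 1.73 and 0.232/0.183 = 1.27, so p<0.05 is expected in about 41% and 25% of trials. Simulation (4,000 trials per setting, t-tests on change as a stand-in for the time-by-condition test) agrees closely:

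| ρ | Gap v non-adherers (SD) | p<0.05 | Gap v control (SD) | p<0.05 |
|---|---|---|---|---|
| 0.1 | 0.17 | 13% | 0.12 | 10% |
| 0.2 | 0.34 | 42% | 0.24 | 26% |
| 0.3 | 0.50 | 75% | 0.35 | 47% |

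**Sensitivity to the assumptions.** A second null simulation used 163 per arm, 20% random attrition, adherence of 10%, 25% or 50%, and the same correlations.
- The spurious gap was 0.16 to 0.58 SD against non-adherers and 0.08 to 0.53 SD against control.
- False findings in favour of adherers arose in 9% to 80% and 7% to 49% of trials, against a nominal 2.5% in that direction.
- At ρ = 0 the error rates were nominal.
- At ρ = −0.2 adherers looked 0.16 to 0.35 SD worse than control.
- Comparing the randomised arms on the same data rejected in 4.6% to 5.6% of trials, which is nominal.

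**Scale.** The within-group effects assumed under Sample size imply 0.35 − 0.10 = 0.25 between self-directed use and psychoeducation. At ρ = 0.2 and 30% adherers, the spurious gap against control is of about that size. This is a rough comparison, because the standardiser behind the protocol's effect sizes is not stated.

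**The case against.** Several points on the other side are sound.

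- **Direction.** A reader might infer that the analysis is bound to credit an inert app with benefit. The documents do not support that. The Background links likelihood of app use to perceived need as well as to beliefs about the app. Greater need could go with slower recovery, and a participant who feels better may stop using the app. The sign is unknown, so the bias can only be stated conditionally.
- **Definition.** A reader might also infer that the adherence measure misclassifies someone who finishes all nine collections in five weeks or works only from the full lesson list. It does not. Adherence is defined as following the instruction given under Interventions, which is weekly, and such a participant did not follow it. Other patterns of use are captured by the 0 to 6 weekly score, the three completion measures and the exploratory usage data.
- **Label.** The mislabelling is confined to one condensed sentence in the Abstract. The statistical methods section introduces the adherence analysis separately, Trial objectives says that the influence of engagement will be explored, and Limitations speaks only of use that goes along with benefit. An analysis plan that is not shown may also add adjustment or caution.

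These points limit the concern but do not remove it. The Abstract still contradicts the methods, and the methods still assign to a non-randomised contrast the task of judging the instructions.

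**Conclusion.** The point holds in a limited form. The intention-to-treat label in the Abstract is wrong by the protocol's own definition, whatever the data show. The three-group model is a non-randomised comparison given a causal task. Its bias could be as large as the effect that the trial hopes to find: at 30% adherers, about 0.17 to 0.50 SD against non-adherers and 0.12 to 0.35 SD against control for correlations of 0.1 to 0.3. These figures rest on an assumed correlation and an assumed adherence rate. They show what could happen and do not predict the result.

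Nothing here touches the primary analysis. Comparison by randomised arm keeps its nominal error rate, and it would be wrong to read this point as a doubt about that result.

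**What to change.** 1. **Abstract.** Take the adherence comparison out of the intention-to-treat sentence and give it its own, for example: *A separate, non-randomised analysis will describe how outcomes differ by adherence.*
2. **Statistical methods section.** Label the three-group model non-randomised and associational, in line with the more careful wording under Limitations. State that it will not be used alone to conclude that the instructions work or need adjusting. Carry the label into the primary outcomes paper.
3. **Optional supplement.** If a causal estimate of app use is wanted, add an instrumental-variable (complier-average type) estimate with allocation as the instrument and an exposure already logged, such as lessons completed out of 37, with the 0 to 6 weekly score as sensitivity. State that allocation is assumed to act only through that exposure. This is open to doubt in both app arms, because of the SMS reminders, the other app features and the active control, and more so in the guided arm because of the chats. The estimate rescales the randomised contrast. It therefore cannot test whether one collection per week is the right instruction, and it should not be presented as doing so.

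Items 1 and 2 cost only wording. Item 3 costs one further analysis of data already collected, with a wider interval than the intention-to-treat result.
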